### Intervention

Training process

The 5 ACCs received a 4 h initial training session about social marketing principles and the healthy lifestyle theory from a university specialist in health and communication. Moreover, the 5 ACCs received 1.30 h of training every week over 12 weeks (1st academic year) and 1.30 h of training every week over 12 weeks (2nd academic year), a total of 12 sessions/academic year, leading to a total of 24 sessions (1.30 h/session), also performed by a university specialist. The aims of the sessions were to train the 5 ACCs on health promotion, health education, communication and social media so that they could design the challenge activities for their peers. The university specialists educated the 5 ACCs about the primary and secondary objectives of the intervention, and the ACCs then had to design the challenges for their schoolmates to accomplish the defined objectives.

The 5 ACCs designed social marketing activities proposed as challenges based on 8 SMBCs: 1) customer orientation, 2) behaviour, 3) theory, 4) insight, 5) exchange, 6) competition, 7) segmentation and 8) methods mix (Table 2). These 5 ACCs were recruited separately from two different high-schools. Then, the 5 ACCs, as peer-led instructors, identified the possible lifestyle components that they and their peers should improve, selected the easiest and most common communication channels among them, and determined which challenges should be designed and implemented for their peers.

**Table 2 Tab2:** Use of SM in the intervention

Research group	Adolescent Challenge Creators (ACCs)	Research group and Adolescent Challenge Creators (ACCs)
*1. Customer Orientation*: Focuses on the audience to help understand their lives, behaviours and issues.	*2. Behaviour*: Aims to change people’s actual behaviours.	3.*Theory*: Uses behavioural theories to understand behaviour and to inform the intervention.
The peer-led model attracts the motivation of adolescents to participate and interact in the intervention, because adolescents prepare activities directed to adolescents. In this way, it has in mind their motivations and behaviours.	Aims to improve the consumption of fruits and vegetables, PA practice, and breakfast consumption and decrease the TV, PC and video game behaviour.	It used the behavioural change framework, taking into account the “Behaviour Change Wheel” (Michie, van Stralen, & West, 2011).
5. *Exchange*: Considers the benefits and costs of adopting and maintaining a new behaviour. The perceived cost can be social, economic, or physical.	4. *Insight*: develop a deep understanding of the target audience.	6. *Competition*: Seeks to understand the possible barriers for the audience’s time, attention, and inclination to behave in a particular way.
The consideration of the cost-effectiveness of the intervention will be evaluated at the end-of-intervention.	The peer-led model motivates adolescents to participate and interact in the intervention because adolescents prepare activities directed towards adolescents. In this way, it has in mind their motivations and behaviours.	The 5 adolescent coordinators discussed the enablers and barriers that adolescents face when making behavioural changes. From this debate, some changes were proposed to facilitate the process by including stakeholders.
*8. Methods Mix*: Uses a mix of methods to bring about behavioural change. Does not rely solely on raising awareness.		7. *Segmentation*: Identifies audience “segments” that have common characteristics and then tailors interventions appropriately.
It contributed to informing using social media, educating using activities designed by adolescent coordinators and social media, and supporting using visual material in high-schools and social media. The design and control will be applied using the suggestions provided by 5 adolescent coordinators.		The intervention is focused on adolescents 13 to 16 years of age who attend the participant high-schools and are from low socioeconomic status neighbourhoods.

Social Marketing National Benchmark Criteria (SMBC) developed by the National Social Marketing Centre (NSMC) UK [23]

b)Design and implementation process

The ACCs chose the name “Som la Pera” for the Spanish intervention. This name is a Catalan idiom that literally means “we are a pear” but figuratively means “we are cool”. The ACCs designed and implemented the following challenges: gymkhanas (an activity inside high-schools in which adolescents were divided by teams and competed among themselves in different sport and food tasting competitions, such as goal scoring, racing, or discerning foods with one’s eyes closed) and cooking ability and lifestyle knowledge competitions (high-school cooking competition to prepare healthy dishes simulating cooking TV show or quiz show), as well as pop-up events that included healthy cooking contests and lifestyle knowledge competitions. The 5 ACCs had to be in touch with community stakeholders to obtain some resources free of charge. For example, Central Mercat de Reus gave them food to develop cooking competitions and run the gymkhana, and local government provided local community spaces to develop challenges. Moreover, material costs for items such as posters, flyers, etc. were paid for by the project budget. The ACCs chose Facebook as the main channel of communication with their peers (https://www.facebook.com/somlapera). The intervention designed by the Spanish ACCs was launched in Reus, Spain, in May 2014.

The 5 challenges designed by the ACCs over the first year in the intervention high-schools were implemented for a period of 12 weeks (second phase Fig. 1). At the end of this phase, there was an EYTO project meeting in London (UK) at which the 5 ACCs from the 4 participating countries came together to exchange experiences and ideas so they could revise, maintain or add new components to their second-year design intervention. The costs of this meeting were included in the project funding (third phase Fig. 1). Five new challenges designed by the ACCs were implemented during the second academic year, for a period of 12 weeks (fourth phase Fig. 1). And finally, last European EYTO meeting in Spain to conclude the participation of the ACCs were done to exchange intervention experiences across participating countries (fifth phase Fig. 1).

In the control group, no intervention will be implemented, but the outcome measurements were collected in parallel with the intervention group.

### Evaluation process

#### Primary and secondary outcomes

The expected primary outcomes of the Spanish intervention were as follows: increases in the consumption of fruits and vegetables and physical activity practice, along with reductions in TV/computer/game console use. The secondary outcomes were as follows: increased breakfast consumption, engagement with local recreation and reduced obesity prevalence. The outcomes of the Spanish intervention were measured by the Health Behaviour in School-aged Children Study (HBSC) Survey 2009–2010 [35] to evaluate the adolescents’ lifestyles at baseline and at the end of the intervention as presented in Table 3. The HBSC study is a validated cross-sectional survey of school students that collects data every four years on 11-, 13- and 15-year-old adolescents [36]. The baseline measurements from the intervention and control groups were performed in the second phase, and the end-of-study measurements were performed in the fourth phase (Fig. 1). Analyses and evaluations of each country’s intervention and global project will be performed in phase 5 (Fig. 1) so that the project can be concluded.

**Table 3 Tab3:** Outcomes measurements in the Health Behaviour in School-aged Children Study (HBSC) Survey

Health Behaviour in School-aged Children Study Items	Outcome measured	Question	Possible answers
Eating habits	Nutritional behaviour. Fruit, vegetable and water consumption.	How many times a week do you usually eat or drink (fruits, vegetables, sweets, coke or other soft drinks that contain sugar)…?	Never, less than once a week, once a week, 2–4 days a week, 5–6 days a week, once a day, every day, every day more than once every day.
(primary outcomes)	Breakfast quantity and quality	How often do you usually have breakfast (more than a glass of milk or fruit juice)?	*Weekdays* (I never have breakfast, one day, two days, three days, four days, five days).
			*Weekends* (I never have breakfast during the weekend, I usually have breakfast on only one day of the weekend (Saturday OR Sunday), I usually have breakfast on both days (Saturday AND Sunday)).
Physical activity	Physical activity practice	Over the past 7 days, on how many days were you physically active for a total of at least 60 min per day?	0 days, 1 day, 2 days, 3 days, 4 days, 5 days, 6 days, 7 days.
(primary outcomes)			
		Outside school hours: How often do you usually exercise in your free time so much that you get out of breath or sweat?	Every day, 4–6 times a week, 2–3 times a week, once a week, once a month, less than once a month, never.
		Outside school hours: How many hours a week do you usually exercise in your free time so much that you get out of breath or sweat?	None, about half an hour, about 1 h, about 2 to 3 h, about 4 to 6 h, about 7 h or more.
Sedentary behaviour	Sedentary behaviour	About how many hours a day you usually watch television (includes DVD and videos) in your free time?	Weekdays: None at all, about half an hour a day, about 1 h a day, about 2 h a day, about 3 h a day, about 4 h a day, about 5 h a day, about 6 h a day, about 7 or more hours a day.
(primary outcomes)			Weekends: None at all, about half an hour a day, about 1 h a day, about 2 h a day, about 3 h a day, about 4 h a day, about 5 h a day, about 6 h a day, about 7 or more hours a day.
		About how many hours a day do you usually play games on a computer or games console (PlayStation, Xbox, GameCube, etc.) in your free time?	Weekdays: None at all, about half an hour a day, about 1 h a day, about 2 h a day, about 3 h a day, about 4 h a day, about 5 h a day, about 6 h a day, about 7 or more hours a day.
		About how many hours a day do you usually use a computer for chatting on-line, internet, emailing, homework, etc. in your free time?	Weekends: None at all, about half an hour a day, about 1 h a day, about 2 h a day, about 3 h a day, about 4 h a day, about 5 h a day, about 6 h a day, about 7 or more hours a day.
Self-confidence	Weight control and body image	At the present, are you on a diet or doing something else to lose weight?	No, my weight is fine; No, but I should lose some weight; No, because I need to put on weight; Yes.
(secondary outcomes)			
Body mass index (secondary outcomes)	Perceived obesity and overweight prevalence	How much do you weigh without clothes?	Free space for answer.
		How tall are you without shoes?	Free space for answer.

Items obtained from the Health Behaviour in School-Aged Children (HBSC) 2009/2010 Ref. [35]

#### Statistical analysis plan

We estimated that with a sample size of 121 adolescent schoolmates per group, the study will have 90 % power to detect a difference of a 0.5 portion of vegetables or fruits between the intervention and control groups, setting the bilateral level of statistical significance at 5 %. We anticipate a loss of follow-up rate of 30 %.

Analyses of the results will be performed on an intent-to-treat (ITT) basis, defined as a participant who had at least baseline efficacy data.

The descriptive results are expressed as the means ± standard deviations and the 95 % confidence intervals for quantitative variables or as frequency distributions for qualitative variables. Generalised linear mixed models are used to analyse differences between the intervention and control groups and changes in primary and secondary outcomes from baseline to the end of the intervention. For the rest of the efficacy variables, we will use Fisher’s exact test for the categorical variables and Student’s *t*-test for the continuous variables. The significance level is fixed at a bilateral level of 5 %.

All statistical analyses are performed with SPSS version 22.0 (SPSS, Inc., IBM, Armonk, NY, USA).

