**Methods/Design:**

In Spain, the research team performed a cluster randomised controlled intervention over 2 academic years (2013–2015) in which 2 high-schools were designated as the control group and 2 high-schools were designated as the intervention group, with a minimum of 121 schoolchildren per group.

From the intervention group, 5 adolescents with leadership characteristics, called “Adolescent Challenge Creators” (ACCs), were recruited. These 5 ACCs received an initial 4 h training session about social marketing principles and healthy lifestyle theory, followed by 24 sessions (1.30 h/session) divided in two academic years to design and implement activities presented as challenges to encourage healthy lifestyles among their peers, the approximately 180–200 high-school students in the intervention group. During the design of the intervention, it was essential that the ACCs used the 8 social marketing criteria (customer orientation, behaviour, theory, insight, exchange, competition, segmentation and methods mix). The expected primary outcomes from the Spanish intervention will be as follows: increases in the consumption of fruits and vegetables and physical activity practice along with reductions in TV/computer/game console use. The secondary outcomes will be as follows: increased breakfast consumption, engagement with local recreation and reduced obesity prevalence. The outcomes will be measured by the Health Behaviour in School-aged Children Study (HBSC) survey at baseline and at the end of the intervention.

In the control group, no intervention was implemented, but the outcome measurements were collected in parallel with the intervention group.

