### Spanish study design

The “Som la Pera” intervention is a school cluster randomised controlled trial. The participating Spanish city was Reus (Catalonia). Local authorities have already identified public high-schools that they agree serve low-income neighbourhoods that are considered disadvantaged areas. From the 9 public high-schools identified in these neighbourhoods, 4 high-schools were randomly selected. The randomisation code was computer generated. The high-schools were assigned to the control or intervention arm at a ratio of 1:1 via an interactive electronic response system hosted by the Nutrition and Health Technology Centre (CTNS) in Reus, Spain. The unit responsible for the randomisation took no further part in the study. Because the researchers know the names of the four high-schools, allocation concealment was not performed. The project consists of five main phases, as shown in Fig. 1. The first phase included the randomisation and allocation of the high-schools in the disadvantaged area into the two intervention and two control high-schools. High-school teachers from the randomised intervention group selected the five adolescents according to their knowledge of the students by considering leadership characteristics and English level (because the students will participate in EYTO European meetings), 2 adolescents from one high-school and 3 from the other high-school. These 5 adolescents will be referred to in this protocol as the Adolescent Challenge Creators (ACCs). The study characteristics are summarised in Table 1.

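### The stated 90 % power from 121 pupils per group shows no allowance for randomising only four schools, and the design does not support it

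*Protocol article*

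**What the plan says.** The Statistical analysis plan section of the protocol article gives the group size first: "We estimated that with a sample size of 121 adolescent schoolmates per group". The claim attached to that number is that "the study will have 90 % power to detect a difference of a 0.5 portion of vegetables or fruits", tested two-sided at 5 %. The section then adds "We anticipate a loss of follow-up rate of 30" %, without saying whether 121 is counted before or after that loss. The abstract repeats the number as a floor: "with a minimum of 121 schoolchildren per group".

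The Spanish study design section says that Som la Pera "intervention is a school cluster randomised controlled trial" and that "The high-schools were assigned to the control or intervention arm at a ratio of 1:1". The abstract gives two intervention and two control schools. Table 4 plans 180–200 pupils per group, and Table 1 plans 80–100 per school.

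The analysis section names generalised linear mixed models for the primary and secondary outcomes. It gives no SD, ICC or design effect, and does not say how many degrees of freedom the treatment comparison has.

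**The concern.** The power statement counts pupils, but the allocation has four units. Pupils in one school share teachers, surroundings and peers, and this intervention works through peers. Their answers are therefore likely to be correlated, and 121 pupils carry less information than 121 independent ones. Separately, with two schools per arm, the between-school variation against which the treatment effect is judged is estimated on 2 degrees of freedom. Neither feature is visible in the stated figure.

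Fruit and vegetable consumption is a primary outcome. A trial labelled as 90 % powered for 0.5 portion invites readers to take a non-significant result as evidence that no such effect exists. If real power is far lower, that reading is wrong.

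**Working it through.** **Inputs from the article.** Difference 0.5; two-sided 5 %; power 90 %; 121 per group; loss 30 %; two schools per arm; enrolment 180–200 per group. **Not given, so assumed:** the SD (1.0 and 1.2, obtained by solving backwards) and the ICC (0 to 0.05).

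**1. Reproducing 121.** For independent pupils, n per group = 2 × (1.960 + 1.2816)² × SD² / 0.5² = 84.06 × SD².
- SD 1.2: 84.06 × 1.44 = 121.05.
- SD 1.0: 84.06, and 84.06 / 0.7 = 120.1, which rounds up to 121 with the 30 % loss included.

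Both readings reach 121, to within rounding, at a round SD with no cluster inflation. The enrolment target fits the first reading: 121 / 0.7 = 173, just under 180–200.

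**2. What four schools do to a 90 % calculation.** A large-sample calculation that returns 90 % has difference / SE = 1.960 + 1.2816 = 3.24, whatever SD and ICC lie behind it. A test on four school means has 2(2 − 1) = 2 df and a critical value of 4.303. The noncentral t with 2 df and noncentrality 3.24 gives power of 43 %.

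Reaching 90 % on 2 df needs noncentrality 6.80. With 121 per arm and ICC 0, that requires SD ≤ 0.5 × √(121/2) / 6.80 = 0.57.

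**3. Power at the planned enrolment.** After 30 % loss, 180–200 per group leaves 126–140, or m = 63–70 per school. With two schools per arm, the design effect is DE = 1 + (m − 1) × ICC and SE = SD × √(DE / m).

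Example: m = 63, ICC 0.02, SD 1.2. DE = 1 + 62 × 0.02 = 2.24; SE = 1.2 × √(2.24/63) = 0.226; 0.5 / 0.226 = 2.21. Power is 60 % (large-sample) or 25 % (2 df).

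| Setting | Reference | ICC 0.01 | ICC 0.02 | ICC 0.05 |
|---|---|---|---|---|
| SD 1.2, 63–70 per school | large-sample | 74–77 % | 60–62 % | 37–38 % |
| SD 1.2, 63–70 per school | 2 df | 32–33 % | 25–26 % | 17 % |
| SD 1.0, 63–70 per school | large-sample | 88–90 % | 76–77 % | 50–51 % |
| SD 1.0, 63–70 per school | 2 df | 41–43 % | 33–34 % | 21–22 % |
| SD 1.2, 60.5 per school (121 per arm) | large-sample | 73 % | 59 % | 37 % |
| SD 1.2, 60.5 per school (121 per arm) | 2 df | 31 % | 25 % | 16–17 % |

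**4. Margin in the enrolment target.** At SD 1.2, where 121 must be analysed, 126–140 absorbs a design effect of 126/121 to 140/121 = 1.04–1.16, that is an ICC of about 0.0007–0.0023. At SD 1.0, where 84 are needed, it absorbs 1.50–1.67, an ICC of about 0.008–0.010. Both margins are in large-sample terms only.

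**The case against.** **The SD is unknown, so the sizing method is not proved.** This stands. With 60.5 pupils per school, a clustered large-sample formula also returns 121 at SD 0.95, 0.81 or 0.60 with ICC 0.01, 0.02 or 0.05. A reader might infer that the document shows clustering was ignored. It does not: a match at round SDs, with no clustering term mentioned, supports a strong inference and no more. An ICC may also sit in a fuller protocol that is not shown. The point does not depend on this, because step 2 holds for any SD and ICC behind a large-sample 90 %.

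**Enrolment exceeds 121.** This stands too, and the table allows for it. On the SD 1.0 reading it matters: at ICC 0.01, large-sample power is 88–90 %, close to the claim. On 2 df it does not rescue the claim: even at ICC 0, 63–70 per school gives at most 60 % at either SD.

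**The 2-df test is not the planned analysis.** The plan names mixed models of change from baseline, and adjustment for baseline may recover part of the loss. That is fair, and the 2-df figures are for an unadjusted comparison of school means. But the printed 90 % does not invoke baseline adjustment. A mixed model can allow for clustering in the analysis, but it does not add schools.

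**At ICC exactly 0 with pupil-level degrees of freedom, 90 % is recovered at the back-solved SDs.** True, but that sets aside the unit of randomisation.

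**Conclusion.** The 90 % claim is not supported for this design and should not stand as written. The firmest result needs no chosen ICC: any large-sample calculation giving 90 % gives about 43 % on an unadjusted school-level test with 2 df. Beyond that, the size of the shortfall depends on an assumed SD (1.0–1.2) and ICC (0.01–0.05). At the planned enrolment and 30 % loss, power runs from 37 % to 90 % by the large-sample formula and from 17 % to 43 % on 2 df.

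A reader might take one of these, such as 25 % at ICC 0.02, as the trial's true power. The documents do not support that: they give neither the SD nor the ICC, and the gain from baseline adjustment is unquantified. Nor does the point mean that the trial must add schools. It means that the trial should not be presented as 90 % powered for 0.5 portion.

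**What to change.** Withdraw the 90 % claim and restate the calculation with:
- the SD actually used;
- an assumed ICC range and the resulting design effect;
- degrees of freedom based on four schools;
- whether 121 is before or after the 30 % loss;
- any credit taken for baseline adjustment, with the correlation assumed.

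Give the design power as a range at the planned 180–200 per group, with every assumption beside it. Add that a null result will not be read as evidence against a 0.5-portion effect, and that interpretation will rest on the estimate and its confidence interval.

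The cost is one paragraph and a less favourable stated power. No schools, pupils or measurements need to be added.

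### The sample size is justified by a 0.5-portion difference, but the only named instrument records how often fruit and vegetables are eaten, and nothing links the two scales

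*Protocol article*

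**What the plan says.** The Statistical analysis plan section of the protocol article justifies the size of the trial in one sentence. The target it names is a "difference of a 0.5 portion of vegetables or fruits between the intervention and control groups". The other inputs are 121 pupils in each arm, 90 % power and a two-sided 5 % level. The next sentence adds an expected 30 % loss to follow-up. This is the only power statement in the article.

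The section on primary and secondary outcomes names the instrument: "The outcomes of the Spanish intervention were measured by the Health Behaviour in School-aged Children Study (HBSC) Survey", in its 2009–2010 form, at baseline and at the end of the intervention. In Table 3 the fruit and vegetable item begins "How many times a week do you usually eat or drink". The answers run through ordered frequency categories, from never, through bands of days per week, to an open category for more than once a day. The Abstract names the same survey for the outcomes, and the schedule in Table 4 lists no other dietary instrument.

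**The concern.** Fruit and vegetable consumption is a primary outcome and the only one on which the trial is sized. The sized effect is a difference in portions, but the survey yields frequency categories. A pupil who eats two portions at one daily sitting and a pupil who eats one portion once a day give the same answer.

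Two things are at stake. First, the 90 % power claim cannot be carried over to the variable that will be analysed. Second, an estimate from the mixed model on the survey item cannot be compared with 0.5 portion unless someone chooses a conversion. If that choice is left until the data are seen, the reading of the result against its target depends on it.

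**Working it through.** **1. The two statements side by side.**

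| | Sample-size sentence | Table 3 item |
|---|---|---|
| Quantity | portions | how often eaten |
| Type | difference between groups, in portions | ordered category, open at the top |
| Link to the other scale | none stated | none stated |

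**2. Can 121 be reproduced on the portion scale?** Inputs from the Statistical analysis plan section: difference 0.5, 121 per group, power 90 %, two-sided alpha 5 %. The 1:1 ratio (of schools) is from the Spanish study design section. No SD is given, so I solve for it with the two-sample normal formula, ignoring clustering:

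SD = 0.5 / [(1.960 + 1.282) × √(2/121)] = 0.5 / (3.242 × 0.1286) = 0.5 / 0.4167 = 1.20 portions.

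Going forward with an assumed SD of 1.2, n = 2 × 3.242² × 1.2² / 0.5² = 121.05, or 122 after rounding up; power at 121 is 90.0 %. If 121 already includes the 30 % loss, about 85 are analysed (121 × 0.7 = 84.7). The implied SD is then 0.5 / [3.242 × √(2/84.7)] = 1.00, and forward 85 / 0.7 = 122.

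The required number per group depends strongly on the unstated SD:

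| Assumed SD (portions) | n per group |
|---|---|
| 0.8 | 54 |
| 1.0 | 85 |
| 1.2 | 122 |
| 1.5 | 190 |
| 2.0 | 337 |

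So 121 is a credible answer to a question posed in portions. It cannot be redone for the survey scale, because the article gives neither an effect nor an SD on that scale.

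**3. What 121 per group detects on something the survey does record.** Take the proportion reporting at least daily intake. The control rate is my assumption, so a range is shown. With p̄ the mean of p1 and p2, I solve for p2 in

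121 = [1.960 × √(2p̄(1−p̄)) + 1.282 × √(p1(1−p1) + p2(1−p2))]² / (p2 − p1)².

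| Assumed control p1 | Detectable p2 | Difference (percentage points) |
|---|---|---|
| 20 % | 38.8 % | 18.8 |
| 30 % | 50.2 % | 20.2 |
| 40 % | 60.7 % | 20.7 |
| 50 % | 70.2 % | 20.2 |

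The detectable difference is about 19 to 21 points across the range. This treats 121 as the number analysed, at one time point, with pupils independent. A clustering allowance would make it larger.

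**The case against.** The best reply is that frequency can be scored. Give each category a number of occasions, take one occasion as one portion, impose a value on the top category, and a mean difference follows. A condensed article may leave such a rule to the full protocol or analysis plan. That stands in part: it defeats any claim that the effect could never be approximated. It does not remove the mismatch, because the article states its target in one unit and its measurement in another, and the scored variable would be a proxy for portions.

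A reader might go further and infer that a shift of 0.5 is invisible on this scale, or needs a jump of a whole category. The documents do not support that, because the target is a difference between groups, not a change in one pupil. As an illustration with assumed midpoints of 3 and 7 times a week, if 12.5 % of pupils moved from the band for two to four days a week to once a day, the mean would rise by 0.125 × 4 = 0.5 per week. Whether 121 per group has power for such a shift is a separate question.

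A reader might also infer a serious ceiling effect from the open top category. The article does not give the share of pupils there at baseline, and the upper answer options are unclear in the text available, so no size can be put on it.

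The missing time unit, the missing SD and the ambiguity over whether fruit and vegetables are taken separately or together are reporting gaps in one short sentence. They are not the error itself. Finally, planned enrolment is 180–200 per group, above 121, but a larger sample does not change the unit.

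**Conclusion.** Wrong as written; should be fixed. The article attaches 90 % power to a quantity that its only named instrument does not record, and states no link between the two scales. The conclusion rests on Table 3 and the sample-size sentence as printed, and on no other dietary measure being named.

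The point is limited to the power justification and to reading the result against 0.5. A reader might infer that the outcome comparison is invalid or that 121 is a miscalculation. Neither follows. Comparing groups on the survey item is not biased by this mismatch, its type I error is not inflated by it, and 121 fits an SD of about 1.2 portions (about 1.0 if the 30 % loss is already included). On the survey scale, the illustrative detectable difference of 19 to 21 percentage points in at least daily intake rests on assumed control rates of 20 to 50 %, 121 analysed per group and no clustering allowance.

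**What to change.** Restate the fruit and vegetable endpoint and the sized effect on the HBSC scale, and give the detectable difference for 121 per group on that scale. Two suitable forms are the proportion with at least daily intake, and the ordered category. Both fit within the generalised linear mixed models already planned, so the analysis method need not change. Say whether fruit and vegetables are analysed separately or together, and give the assumed control distribution with a range.

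If the portion target is to be kept, state before the data are seen how each category is scored, including the value for the top category and the time unit, and label the result a proxy for portions.

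Either route costs a text change and one recalculation, with no new data. The price is that the stated detectable effect becomes coarser than half a portion suggests.

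### With two schools per arm the comparison has 2 degrees of freedom, so the stated 5 % level and 90 % power cannot both hold once schools differ at all

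*Protocol article*

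**What the plan says.** The section on the Spanish study design states that the "intervention is a school cluster randomised controlled trial", and that "The high-schools were assigned to the control or intervention arm at a ratio of 1:1". The abstract gives the count: "2 high-schools were designated as the control group and 2 high-schools were designated as the intervention group".

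The Statistical analysis plan section fixes three things:

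- Method: "Generalised linear mixed models are used to analyse differences between the intervention and control groups", and also changes from baseline to the end of the intervention.
- Level: "The significance level is fixed at a bilateral level of 5" %.
- Size: 121 pupils per group, for which the section claims that "the study will have 90 % power to detect a difference of a 0.5 portion of vegetables or fruits". A 30 % loss to follow-up is anticipated.

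The section gives no SD, ICC or design effect. It does not say which degrees of freedom or reference distribution the mixed model will use. The article says elsewhere that the trial follows the cluster extension of CONSORT.

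**The concern.** Schools were allocated, so the arm effect is judged against variation between schools. Four schools in two arms leave 2 degrees of freedom for that variation, however many pupils each school contributes. The level and the power are both stated as though pupils were the independent units.

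At stake is the error rate of the main conclusion. Under a pupil-scale reference, a significant result may reflect which schools fell into which arm. Under a school-scale reference, the trial has far less chance of detecting 0.5 portion than the article states. Two schools per arm is settled in this document, and later analysis wording cannot add between-school information.

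**Working it through.** **Inputs.** From the article: 2 + 2 schools, two-sided 5 %, 90 % power, difference 0.5 portion, 121 pupils per group, 30 % loss, 180–200 enrolled per arm. Pupils per school, m, is about 60 (121/2) or 90 (180/2). Assumptions: SD back-solved, ICC from 0 to 0.05, equal school sizes, one continuous outcome.

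**Step 1: reproduce 121.** For two independent means, n = 2·SD²·(1.960 + 1.282)²/0.5². Solving for the SD at n = 121 gives 0.5·√(121/2)/3.242 = 1.20 portions. With SD 1.20 the formula returns 121, with no cluster allowance needed. Allowing for loss, 121/0.70 = 173, which fits 180–200 enrolled per arm.

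**Step 2: the reference distribution.** Between-school df = 4 − 2 = 2. The critical value is t(0.975; 2) = 4.303, against 1.96 for a normal reference. A 2-df statistic judged at 1.96 has true two-sided size 0.189.

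**Step 3: level.** Simulation under no effect, at least 200,000 trials per setting. The mixed model has a random school intercept, with its variance bounded at zero.

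| m | ICC | Mixed model, residual df | Mixed model, Satterthwaite df | t-test on 4 school means, 2 df | School variance estimated as 0 |
|---|---|---|---|---|---|
| 60 | 0 | 3.6 % | 3.1 % | 5.0 % | 63 % |
| 60 | 0.01 | 7.6 % | 5.7 % | 5.0 % | 46 % |
| 60 | 0.02 | 10.4 % | 6.9 % | 5.0 % | 36 % |
| 60 | 0.05 | 14.4 % | 7.4 % | 5.0 % | 21 % |
| 90 | 0.01 | 9.0 % | 6.3 % | 5.0 % | 41 % |
| 90 | 0.02 | 12.2 % | 7.4 % | 5.0 % | 30 % |
| 90 | 0.05 | 15.9 % | 7.1 % | 5.1 % | 16 % |

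Rejection rises as zero-variance estimates become rarer. Without the bound at zero, size under the 1.96 cut-off is 18.9 % at every ICC. So the cause is a large-sample reference applied to a 2-df statistic. Zero-variance estimates pull the error down.

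**Step 4: power of the 2-df test.** Standard error of the arm difference = SD·√(DE/m), with DE = 1 + (m − 1)·ICC. The non-centrality is 0.5 divided by this.

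- m = 60, ICC 0: SE = 1.2·√(1/60) = 0.155, non-centrality 3.23, power 0.43.
- m = 60, ICC 0.02: DE = 2.18, SE = 0.229, non-centrality 2.19, power 0.25.
- m = 90, ICC 0: SE = 0.126, non-centrality 3.95, power 0.56.
- m = 90, ICC 0.02: DE = 2.78, SE = 0.211, non-centrality 2.37, power 0.28.

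At ICC 0.05 power is 0.16 (m = 60) and 0.17 (m = 90). The value of about 0.43 at 121 per group does not depend on the back-solved SD. Any large-sample calculation that gives 90 % power implies a non-centrality of 3.24, whatever SD or ICC went into it.

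**Step 5: can both hold?** With the 2-df test, power is below 0.90 everywhere. With Satterthwaite df, power at ICC 0 is 0.58 (m = 60) or 0.65 (m = 90). With residual df, ICC 0.005 already gives level 5.8 % and power 0.75 (m = 60), or 6.5 % and 0.86 (m = 90). The one setting in which both hold is residual df with ICC exactly 0 and 90 analysed per school (level 3.8 %, power 0.93).

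**Step 6: the mixed-model contrast referred to t(2).** This is not the school-mean test. When the school variance is estimated as zero, the standard error is the pupil-level one, which is larger than the school-mean one. At ICC 0.02 its size is 0.2 % (m = 60) or 0.4 % (m = 90), not 5 %.

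**The case against.** The strongest objection is that the article states a level and a class of model, but no critical value. A t-test on 2 df is also a 5 % test. A condensed article may leave the random effects and the df method to a full analysis plan, and Satterthwaite df would keep the level at about 3–7 %. This stands. A reader might infer that the planned analysis is known to over-reject, but the documents do not support that: the inflation is conditional on an unstated reference and on a positive ICC.

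Three other stronger readings also go too far:

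- That zero-variance estimates cause the inflation. The simulation shows the opposite.
- That the authors make a confirmatory claim. The article does not use the word. It names primary outcomes, a 5 % level and 90 % power, and no more can be said.
- That the analysis ignores school. Mixed models are named and cluster reporting standards are cited, so error rates for an analysis without a school term do not describe this plan.

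The simulation is also simpler than the trial. The survey items are ordinal, the schools have 3 or 4 classes per level, and every ICC is assumed. These limits affect the exact percentages but not the 2 degrees of freedom.

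The objection does not remove the conflict between the level and the power, because both are stated here for a design fixed at two schools per arm.

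**Conclusion.** The point holds in conditional form. A large-sample or residual-df reference gives null rejection of about 8–16 % at ICCs of 0.01–0.05 with a school intercept, and no over-rejection at ICC 0. A 2-df school-level test keeps 5 %, but its power is 0.43–0.56 at best and 0.25–0.28 at ICC 0.02. For every ICC examined from 0.005 upwards, no reference considered gives both 5 % and 90 %. The only escape is to assume no school variation whatever, which four schools cannot verify.

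The df count is exact. The inflation figures rest on the assumed ICCs and the balanced continuous model, and the power figures away from 121 per group at ICC 0 also rest on the SD of 1.20. The point warrants correction because the error rate of the primary conclusion, or the stated power, must be wrong as soon as schools differ.

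**What to change.** 1. Make the primary test an unpaired t-test on the four school mean changes, referred to t with 2 df, with its 2-df 95 % interval. Use no school-level covariate, since it would take one of the two degrees of freedom.
2. The mixed model with a school random effect may supply the point estimate. Do not refer its contrast to t(2) as an equivalent test, because it is far too conservative when the school variance is estimated as zero.
3. Report the result as an effect estimate limited by four schools, not as a stand-alone significance claim.
4. Restate the power on 2 df with the SD and ICC given, or withdraw the 90 %.

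This needs no new schools or data. The cost is precision and strength of claim. If the standard error is estimated at its true value, the 95 % half-width with 60 per school is 4.303 × 0.155 = 0.67 portion at ICC 0 and 4.303 × 0.229 = 0.99 at ICC 0.02. Both exceed the 0.5 portion that the trial was sized to detect.
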